## Abstract

**Background:**

Long-term adherence to exercise is often poor for people with coronary heart disease (CHD) who have completed supervised, centre-based cardiac rehabilitation. The aim of this study is to assess the feasibility of a remotely prescribed, delivered and monitored cardiac rehabilitation intervention using a wearable device to support long-term adherence to exercise and physical activity during maintenance of cardiac rehabilitation.

**Methods:**

After completing cardiac rehabilitation, 30 participants with CHD, will be randomised (1:1) to an intervention (*n* = 15) or a usual care group (*n* = 15) in a 12-month feasibility randomised controlled trial (RCT). The intervention will comprise of an exercise consultation, personalised exercise prescription delivered via a wearable activity monitor using biometric feedback, regular monitoring via check-ins, and feedback text-messages for 6-months. Participants will be assessed at baseline (following completion of cardiac rehabilitation) and at three-, six-, and 12-months post-randomisation. The primary outcome will be feasibility, including assessment of eligibility, recruitment, adherence, and acceptability. Secondary outcomes will include exercise capacity, physical activity behaviours, cardiovascular disease risk and quality of life. Semi-structured interviews will be conducted at three-, six-, and 12-months post-randomisation (and with those who drop-out) to explore the acceptability of the study intervention and procedures. A questionnaire will be offered to those who decline participation.

**Discussion:**

The MAINTAIN study will evaluate the feasibility of conducting a future definitive multi-centre RCT testing a remotely prescribed and monitored long-term mHealth maintenance exercise programme, versus usual care, for people with CHD who have completed cardiac rehabilitation.

**Trial registration number:**

ClinicalTrials.gov, NCT05292287. Registered on 22/03/2022

## Introduction

Approximately 2.3 million people in the UK are living with coronary heart disease (CHD), requiring long-term management and support.^1^ This costs in excess of £7 billion in the UK, highlighting not only a personal cost for those affected but also a substantial economic burden.^2^ Long-term management of CHD is multi-faceted, including a combination of medical, pharmacological and lifestyle interventions such as cardiac rehabilitation (CR),^3^ all of which are recommended by the National Institute for Health and Care Excellence (NICE).^4^

Home and centre-based exercise rehabilitation programmes can improve exercise capacity, cardiovascular disease risk markers, quality of life and psychological health in the short- to medium-term.^5,6^ Home-based CR is also considered a safe alternative to centre-based CR.^7-9^ However, physical activity (PA) and exercise discontinuation after supervised CR can have detrimental effects on health, leading to a higher risk of recurrent cardiovascular events, hospitalisation, and premature mortality.^10^ To prevent these negative health outcomes, discharge plans are created on completion of CR which include advice on maintaining PA and exercise as a key part of secondary prevention models.^11,12^ However, due to limited resources, long-term plans are often difficult to implement with direct supervision or follow-up. Consequently, long-term adoption of favourable PA and exercise behaviours is rarely successful, with sporadic maintenance of health-outcomes in cardiovascular disease.^13,14^

Whilst centre-based CR is “gold-standard” there are often barriers to attending, including time availability, transport, travelling distance, financial responsibilities, and work and family commitments.^15^ Alternatively, home-based CR may provide many benefits such as an increased capacity to deliver CR, the potential to personalise programs, and the ability to be more flexible with scheduling and to remove the barriers associated with travelling to CR centres.^7^ Furthermore, the COVID-19 pandemic and subsequent government-enforced lockdowns and social distancing measures have been detrimental to PA participation and almost half of CR services halted all rehabilitation.^16,17^ During this time, face-to-face CR was suspended, which increased the demand for remotely monitored and prescribed home-based exercise programs using telephone calls and/or live video conferencing, often referred to as mHealth.^17-19^ To improve the effectiveness of these programmes, wearable activity devices, providing biometric feedback on a range of variables, can be used to support personalised exercise prescription.^20,21^ These devices may also support improvements in cardiometabolic risk factors, such as inactivity, systolic blood pressure and low-density lipoprotein cholesterol.^22,23^ When combined with personalised text messages from health professionals, wearable activity monitors are often more effective at improving exercise and PA behaviour.^24,25^ Thus, remotely monitored and prescribed CR programs supported by wearable activity monitors may be a feasible alternative or adjunct to centre-based CR during pandemic scenarios.^21^ Two pilot randomised controlled trials (RCTs)^26,27^ reported the potential of wearable activity monitors to support PA maintenance, but only for a period of eight-12 weeks. Whilst wearable activity monitors have been associated with higher short term exercise adherence in clinical populations, longer-term data are sparse and less convincing.^28^ Thus, understanding the effectiveness of long-term home-based CR maintenance programmes using mHealth is ever more essential to overcome both traditional and recently emerging barriers to centre-based CR.

### Rationale for a randomised controlled trial

To improve quality of life and other health outcomes, emerging mHealth technologies may help to bridge the gap between CR teams and people with CHD in the long-term maintenance phase of CR. Assessing the ability of novel mHealth-assisted prescription and monitoring of personalised exercise may help to reduce secondary cardiovascular disease risk, when transitioning from supervised to independent exercise. Despite the potential for long-term benefit, it is equally important to consider the acceptability of these technologies from the perspective of the patient. Furthermore, previous research has not tested newer wearable devices which can ‘coach’ the user by remotely delivering exercise programmes in real-time, ensuring that the correct intensity, duration, and technique are achieved with the support of haptic feedback. This capacity to deliver immediate feedback to the user, whilst data are synchronised to an online web platform accessible to an exercise physiologist, may help people to maintain the PA and exercise behaviours achieved during CR.^29^ Consequently, for people with CHD, a feasibility RCT is needed to evaluate a long-term remotely prescribed and monitored exercise intervention supported by a wearable activity monitoring device providing real-time biometric feedback.

The reMote mAINTenance cArdiac rehabilItatioN (MAINTAIN) study aims to investigate the feasibility of conducting a full-scale RCT testing a remotely prescribed and monitored long-term maintenance exercise programme supported by mHealth, compared to usual care, for people who have recently completed supervised or home-based centre-based CR.

### Objectives

Conduct a randomised feasibility study with 30 participants randomised (1:1) to a remotely prescribed and monitored exercise intervention or usual care. Process-related measures will include eligibility, recruitment, and adherence to the intervention. Physiological, clinical, and health-related measures will include functional capacity and health-related quality of life (HRQoL).Conduct a qualitative analysis to explore the views, perceptions, acceptability, and experiences of participants regarding the remotely prescribed and monitored exercise intervention and all trial procedures.

## Methods

### Study design

The MAINTAIN study is a single centre, assessor blind, feasibility RCT, including a qualitative sub-study. The Standard Protocol Items: Recommendations for Interventional Trials (SPIRIT) guidelines were followed to develop this protocol.^30^

### Study setting

Recruitment will be carried out at an outpatient community CR centre at University Hospitals Coventry & Warwickshire (UHCW) NHS Trust (Figure 1). The study summary according to the World Health Organization (WHO) Trial Registration Data Set is outlined in Table 1.

**Figure 1. fig1-20552076231152176:**
[figure not shown]
Schedule of enrolment, interventions, and assessments.

**Table 1. table1-20552076231152176:** World health organization trial data set.

Data category	Information
Primary registry and trial identifying number	NCT05292287
Date of registration in primary registry	22/03/2022
Secondary identifying numbers	REC reference: 21/LO/0705 IRAS Number: 302243 Protocol number: P121990
Primary sponsor	Coventry University [name] [contact]
Secondary sponsor	N/A
Contact for public queries	Email: [contact]
Contact for scientific queries	[name] Centre for Sport, Exercise and Life Sciences Research Institute for Health & Wellbeing Coventry University [name] Email: [contact]
Public title	Long-term CR using remote exercise prescription and monitoring via a wearable device
Scientific title	reMote mAINTenance cArdiac rehabIlitatioN (MAINTAIN): a randomised controlled feasibility study
Countries of recruitment	England
Health condition(s) or problem(s) studied	Coronary heart disease
Intervention(s)	Intervention group: initial exercise consultation; personalised exercise prescription delivered via a Polar Ignite watch; monitoring via check-ins and feedback text-message support. Control group: usual care
Key inclusion and exclusion criteria	Inclusion: Coronary heart disease; Completed a community centre-based CR programme; clinically stable (symptoms and medication), access to a smartphone with Bluetooth capacity or a computer/laptop/tablet; able to walk unaided; able to provide informed consent. Exclusion: Absolute contra-indications to exercise as per international clinical guidelines ^31^; Any serious mental health/cognitive issue that will prevent engagement with study procedures or increase the risk of exercise complications; atrial fibrillation or other arrhythmia preventing accurate heart rate monitoring; allergies to the watch materials
Study type	Type: feasibility, interventional, single centre Allocation: randomised Assignment: parallel Masking: outcomes assessor
Date of first enrolment	TBC
Target sample size	30
Recruitment status	Ready to start recruitment
Primary outcome(s)	Feasibility and process-related outcomes: number of patients screened, eligible, recruited, randomised, withdrawn, and retained; adherence to a remotely prescribed and monitored exercise programme; physiological, clinical, and patient-reported outcomes to identify a primary outcome for a definitive trial; acceptability of the interventions and trial procedures via qualitative interviews
Key secondary outcomes	At baseline, three-, six- and 12-months post-randomisation: exercise capacity – incremental shuttle walk test (ISWT); physical activity and sedentary behaviour – Actigraph GT3X + ; cardiovascular disease risk – SMART (Second Manifestations of ARTerial disease) risk score (history, smoking, blood pressure, full lipid profile, estimated glomerular filtration rate (eGFR), and high-sensitivity C-reactive protein (hsCRP); HRQoL – MacNew Quality of Life Questionnaire; depression – Patient Health Questionnaire (PHQ-9); anxiety – Generalised Anxiety Disorder 7-Item Scale (GAD-7); self-efficacy – General Self-Efficacy Scale (GSE); activation – patient Activation Measure (PAM); health utility – EQ-5D-5L; health and social care resource use – Client Service Receipt Inventory (CSRI); adverse and serious adverse events. Monthly: Exercise - Godin Leisure Time Exercise Questionnaire

### Eligibility criteria

Table 1 presents the inclusion/exclusion criteria for people with CHD that are eligible to participate in the planned feasibility RCT.

### Participant identification, recruitment, and informed consent

Potential participants will be identified from existing supervised or home-based CR attendees at UHCW NHS Trust by the clinical team on site (Figure 1). Screening logs will be completed when assessing eligibility, and reason(s) for non-participation will be recorded beginning on the 30^th^ of March 2022 until 30 participants are randomised. Potential participants will be approached by the clinical team either in person, or via phone call, email, or post. Those who are interested will be given information about the study verbally and in a printed participant information leaflet. Once willingness to participate has been confirmed, the participant will be asked to attend a baseline assessment to confirm eligibility and complete written informed consent.

### Randomisation, allocation concealment, and blinding

Following completion of all baseline outcome measures, participants will be randomised to the intervention or control arm on a 1:1 ratio using a computer-validated randomisation system (Sealed Envelope Ltd, www.sealedenvelope.com) independent of the researchers to maintain allocation concealment according to the SPIRIT guidelines.^25^ The MAINTAIN intervention and semi-structured interviews will be completed by a researcher (FD) who will not be blinded to group allocation. All follow-up outcomes will be collected by research staff (AW) not involved in intervention delivery and will be blinded to group allocation. Participants will be asked not to inform the follow-up outcome assessor of their allocation.

### Control intervention: usual care

Participants randomised to usual care will not receive any trial-related treatment or support. Usual care at a CR exit assessment will involve an agreed exercise and physical activity plan from an exercise physiologist to maintain their lifestyle behaviour changes. After completing all the follow-up assessments, however, they will be offered a wearable activity device used in this RCT (Polar Ignite©, Polar Electro Oy, Kempele, Finland) along with the device instruction manual to keep.

### The MAINTAIN intervention

*Pre-intervention.* Participants randomised to the intervention arm will receive a participant pack by post including a Polar Ignite watch (figure 2) and set up instructions to download the ‘Polar Flow- Sync & Analyze’ mobile application or the ‘Polar FlowSync’ data transfer software (https://flow.polar.com/start). Participants will log into an account created by the researcher using the participant's email address and password known only to the participant and researcher. Participants will link their ‘Polar flow’ account to the ‘Flow for Coach’ group to allow the researchers to remotely prescribe and monitor PA and exercise. To extract participant data from the watch, Polar accounts will be linked to the research team using an application programming interface.

**Figure 2. fig2-20552076231152176:**
[figure not shown]
The polar ignite watch used in the intervention arm.^32,33^.

*Exercise Consultation.* Each participant in the intervention arm will meet (either in person or via video call) with a clinical exercise physiologist to plan their exercise prescription in accordance with clinical guidelines and personal preferences.^34^ The Polar Ignite^©^ and Polar Flow application functions will be explained and demonstrated to ensure participants are confident using the technology. They will also be signposted to behaviour change resources and diagnosis-specific educational information from the British Heart Foundation (https://www.bhf.org.uk/informationsupport). Following this consultation, the exercise physiologist will schedule the participant's agreed prescription into the online platform.

*Exercise prescription, delivery, and biometric monitoring*. Prescribed exercise sessions will be visible to the participant on the provided fitness watch and on the web or application service. Participants who will perform bodyweight or resistance exercise will be sent guidance using Physiotec (Physiotec HEP, 1996-2022), accessible via an email link, or printed, to ensure exercises are completed safely and effectively without supervision. Participants will be advised to follow the agreed exercise programme and adhere to the watch's haptic vibration feedback to guide heart rate and duration. All data produced during the sessions will be stored on the watch for subsequent synching to the polar flow platform following each exercise session.

*Individualised exercise prescription.* For participants in the intervention arm, exercise prescriptions will be personalised based on outcome assessments, exit assessments of the community CR programme, and exercise data collected during CR. Target heart rates will be based on heart rate prescriptions followed during the participant's phase III CR, calculated by taking into consideration beta-blocker medication and responses on the 6–20 Borg rating of perceived exertion (RPE) scale to monitor intensity. All exercise sessions will include a warm-up and cool-down. Initially, participants will be advised to exercise at least twice per week, progressing to the recommended ≥3 sessions per week as tolerated in accordance with the Association of Chartered Physiotherapists in CR.^35^

*Check-ins.* At the end of the first-month post-allocation/randomisation, participants will attend a check-in with an exercise physiologist either in person or via video or telephone. Data will be reviewed to progress exercise and PA behaviour through goal setting, whilst troubleshooting any issues. The participant's exercise programme will be updated for months two and three. Subsequent check-ins will take place at the beginning of month four, providing updated goals and exercise prescriptions for months four to six, and at the beginning of month seven, updating goals and exercise prescriptions for months seven to 12 of the intervention. At the final check in, instructions for creating and developing a polar flow training plan, either via a web service or via the Polar Flow application, will be provided to encourage participant independence. Plans to overcome individual barriers will be discussed to create an action plan.

*Remote exercise monitoring.* Participants will be advised to synchronise the watch daily and will be asked to wear the watch according to the manufacturer's recommendations whilst exercising. The watch display will guide participants through exercise sessions, whilst simultaneously collecting the exercise data. Following each exercise session, participants will be instructed to synchronise the watch with the Polar Flow application, rate the perceived load of the session based on an RPE from one to 10 (1 classified as ‘very, very easy’, and 10 classified as ‘maximal’), use a five-point Likert scale to rate how they feel, and provide feedback on the exercise session's intensity, duration, and their enjoyment levels. Participant responses will guide text message feedback.

*Personalised text message feedback*. Personalised text message feedback will be gradually tapered between months one, two-three, four-six, and seven-12. Initially messages will be sent after every session, reducing to weekly, biweekly, and then ceasing, respectively. Two-way conversation will be possible between the exercise physiologist and the participant to troubleshoot any issues. Participants completing ≥2 sessions will receive positive feedback text messages. Those completing one session per week will receive positive feedback, but with additional encouragement to complete ≥2 sessions. Participants who have not completed any sessions over a two-week period will receive a text message asking if they need support, and the exercise prescription will be amended accordingly following breaks in training. Participants will also be able to complete and record additional unprescribed ad-hoc exercise sessions.

*Theoretical behavioural underpinning:* The intervention is designed based on the principles of the COM-B model of behaviour change (capability, opportunity, motivation, and behaviour)^36^ with embedded behaviour change techniques. In the context of this study, capability is addressed by increasing the participant's confidence when completing remotely monitored exercise sessions, and by identifying key barriers and how to overcome them during the initial exercise consultation. The provision of British Heart Foundation educational resources will provide knowledge on risk factors. Opportunity relates to removing the barrier of travelling to a centre to exercise, as well as the provision of feedback text messages and prompts from the watch to exercise. Motivation will be addressed using goal setting and feedback text messages.

### Safety

The exercise physiologist delivering the intervention will be an experienced CR practitioner. The assessments will be performed in a cardiopulmonary rehabilitation centre with appropriately trained staff and emergency equipment. Condition-specific monitoring of exercise responses, as per cardiopulmonary rehabilitation guidelines will reduce and manage risk.^31^ The remotely prescribed and monitored exercise and lifestyle PA will replicate exercise performed during the participant's CR programme.

### Outcome measures

*Primary outcome –* feasibility and process related measures:
The number of patients screened, eligible, recruited, randomised, withdrawn, and retained.Adherence to the intervention in relation to the number of prescribed exercise sessions completed at the prescribed intensity/duration.Physiological, clinical, patient-reported outcomes to identify a primary outcome for a future definitive RCT.Acceptability of the intervention and trial procedures via qualitative analysis of semi-structured interviews.*Secondary outcomes.* Physiological, clinical, and participant-reported outcomes will be assessed at baseline, and at three-, six-, and 12-months post-randomisation for both the intervention and control arms (Figure 3). Questionnaires will be completed using Qualtrics (Qualtrics, Provo, UT) or a paper version.

**Figure 3. fig3-20552076231152176:**
[figure not shown]
MAINTAIN feasibility randomised controlled trial flow chart.

### Assessments

Exercise capacity will be assessed with the Incremental Shuttle Walk Test (ISWT).^37^ This involves a 10-m shuttle walk at a steady pace to the timing of an audio track until the participant cannot maintain the required speed. RPE, heart rate and symptoms will be monitored throughout.

PA and sedentary behaviour will be assessed with an Actigraph wGT3X + triaxial accelerometer, worn on a belt around the waist during waking hours for seven days after each follow-up timepoint. This device is reliable in the measurement of PA at various intensities, and sedentary behaviour, during free-living conditions.^38,39^ Exercise time and intensity will be assessed monthly using the Godin Leisure Time Questionnaire (GLTEQ).^40^

Cardiovascular disease risk will be evaluated using the Second Manifestations of ARTerial disease (SMART) risk score.^41^ The score accounts for medical history, smoking status, blood pressure, full lipid profile, estimated filtration rate and high-sensitivity C-reactive protein. Blood samples (5 mL) will be collected using standard venepuncture techniques. Participants will be asked to refrain from participating in exercise for 24 h. Serum will be separated by centrifuging samples at 3000 rpm for 10 min before being aliquoted and frozen at −80 °C. Following analysis samples will be disposed of in accordance with the UK Human Tissue Act.

Disease specific HRQoL will be measured using the MacNew Quality of Life Questionnaire,^42^ which is a reliable and valid questionnaire to assess HRQoL in people with CHD. Depression will be assessed with the Patient Health Questionnaire (PHQ-9)^43^ which is a valid nine item questionnaire,^44^ and anxiety will be measured using the Generalised Anxiety Disorder 7-Item Scale (GAD-7),^45^ which is a self-report questionnaire comprised of seven items, valid for measuring generalised anxiety disorder. Self-efficacy will be assessed using the general self-efficacy scale (GSE),^29^ which is a 10-item psychometric scale designed to assess optimistic self-beliefs to cope with a variety of difficult demands in life. Patient activation, a measure of how able a person can manage their own health, will be assessed with the Patient Activation Measure^®^ (PAM^®^),^46^ a valid and reliable questionnaire useful at an individual level across a range of chronic conditions.

Health utility will be measured using the EQ-5D-5L^47^ questionnaire, which is a validated, generic HRQoL measure consisting of five dimensions to create a health utility score. Health and social care resource use will be assessed using an adapted Client Service Receipt Inventory to examine the feasibility of collecting these data and refine resource use schedules for a definitive RCT. The cost of delivering the intervention will be recorded, including staffing, facility, consumables, etc. To assess the safety of the MAINTAIN trial, adverse events (AEs) and serious adverse events (SAEs) will be monitored in accordance with the principles of Good Clinical Practice.

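### On the nominal calendar, the 3- and 6-month accelerometer weeks coincide with check-ins and text-message step-downs in the intervention arm only, so they sample a transition, not the phase just completed

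*Protocol article*

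**What the plan says.** The Outcome measures section sets the follow-up assessments "at three-, six-, and 12-months post-randomisation for both the intervention and control arms". The Assessments section then has the accelerometer "worn on a belt around the waist during waking hours for seven days after each follow-up timepoint", so each wear week begins at the timepoint and runs forward from it.

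The check-ins are described under The MAINTAIN intervention. The first is dated from randomisation: "At the end of the first-month post-allocation/randomisation, participants will attend a check-in". The next is placed as follows: "Subsequent check-ins will take place at the beginning of month four, providing updated goals and exercise prescriptions for months four to six". The last comes "at the beginning of month seven, updating goals and exercise prescriptions for months seven to 12 of the intervention". None is scheduled at 12 months.

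Text support changes at the same boundaries: "Personalised text message feedback will be gradually tapered between months one, two-three, four-six, and seven-12". Frequency goes from weekly to biweekly at month four and from biweekly to none at month seven.

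The control arm has no counterpart to any of this: "Participants randomised to usual care will not receive any trial-related treatment or support".

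On blinding, the Randomisation section relies on participants' discretion: "Participants will be asked not to inform the follow-up outcome assessor of their allocation". The Polar watch is issued to the intervention arm at the start and offered to controls only once all follow-up assessments are complete.

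**The concern.** The trial is about maintaining activity after cardiac rehabilitation. A reading labelled 3-month or 6-month should describe the behaviour reached by the end of the support phase that led up to it. If the wear week starts where that phase ends, and the intervention arm's goals, prescription and text frequency change at that moment, the reading describes the start of the next phase in one arm and an ordinary week in the other.

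The accelerometer is the only device-based measure of free-living activity and sedentary time taken in both arms. The article intends the secondary outcomes to help identify the primary outcome of the definitive trial and to inform its sample size. An activity difference that partly reflects a recent contact, or a recent withdrawal of texts, would be a poor guide to either.

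A smaller, related matter arises at the same visits. A watch that only one arm owns could reveal allocation to the blinded assessor without the participant saying anything.

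**Working it through.** No figure in the plan bears directly on this point, so the check sets the schedules on one timeline. It assumes that the month count for the later check-ins starts at randomisation, as is stated for the first, and takes a month as 365.25 / 12 = 30.44 days.

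**Wear weeks as written** (timepoint to timepoint + 7 days)
- 3 months: 3 × 30.44 = day 91.3, so days 91.3 to 98.3.
- 6 months: 6 × 30.44 = day 182.6, so days 182.6 to 189.6.
- 12 months: 12 × 30.44 = day 365.2 (365.25 unrounded), so days 365.2 to 372.2.

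**Intervention-arm events**
- First check-in, end of month one: day 30.4.
- Start of month four = end of month three = day 91.3: check-in, and texts go from weekly to biweekly.
- Start of month seven = end of month six = day 182.6: check-in, and texts stop.
- Near day 365: no check-in and no change in texts.

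**Nominal time from the latest check-in to the start of the wear week**
- 3 months: 91.3 − 91.3 = 0 days.
- 6 months: 182.6 − 182.6 = 0 days.
- 12 months: 365.2 − 182.6 = 182.6 days.

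So the 3-month week lies in the months four-to-six phase and the 6-month week in the months seven-to-12 phase. The three readings are also not alike in their distance from contact.

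**If the week were moved** to end one day before the visit, it would run from 8 days to 1 day before the timepoint: days 83.3 to 90.3, 174.6 to 181.6 and 357.2 to 364.2. Each would then lie wholly within the phase that it is meant to describe.

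**Illustration of why placement can matter.** This is an assumption throughout; the article gives no activity trajectory. Suppose that a check-in adds a boost of size 1 that decays with half-life h, and let k = ln 2 / h. The mean over the first week is (1 − e^(−7k)) / (7k). The mean over an interval of L days is (1 − e^(−kL)) / (kL). The mean over the last week is the first-week mean × e^(−k(L − 7)). With L = 91.3 days and h from 7 to 56 days:
- first week: 0.72 to 0.96
- whole interval: 0.11 to 0.60
- last week: 0.00 to 0.34

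This shows only that the week chosen can matter if such a boost exists. It leaves out the simultaneous loss of text support, which could act the other way, so it does not estimate a net effect.

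**The case against.** The strongest reply is that the article fixes neither the order nor the gap. The start of a month is not a day, and a check-in held after the wear week would remove the overlap. Visit sequencing is also the kind of detail that a journal article leaves to the full protocol, and the schedule figure and flow chart, which could not be read for this review, may settle it. This stands in part: the coincidence is one of nominal calendars. It is weakened by the check-in text itself. The first check-in sets the programme only for months two and three, so delaying the next beyond the wear week would leave that week without a scheduled prescription.

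A reader might infer that activity is caught at an artificial peak, that the bias favours the intervention, and that a false decline to 12 months will follow. The article does not support this. Text feedback falls at the very same boundaries, most clearly at month seven when it ends, so the net effect could go either way. Check-ins are also part of the intervention, and a fall after support ends may be a real loss of effect, which is what a 12-month study should see. Nor can the distortion be expressed as a share of the 0.5 effect size in the Sample size section: any lift would have to be assumed, and that 0.5 has no stated metric and is not tied to accelerometry.

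The week before a check-in is itself the point furthest from contact, and under the decay assumption it samples a trough. That is fair, but it is the end of the phase being reported, and it suits a question about maintenance.

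The stakes are limited. Accelerometry is one of many secondary outcomes in a 30-person feasibility trial that disclaims formal hypothesis testing, and the shuttle walk test and the monthly Godin questionnaire also inform on exercise. The questionnaire, however, is self-reported, and the walk test measures capacity, not free-living activity.

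On blinding, the watch is to be worn while exercising; nothing says that it is worn at assessment visits. Unblinding would hardly affect a free-living accelerometer record. It remains only a possible leak at an assessment that includes a walk test.

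**Conclusion.** The point holds as a cheap improvement. On the nominal calendar, the accelerometer weeks at two of the three follow-ups coincide with a check-in and a step-down in texts that only the intervention arm has. The 3- and 6-month activity differences would therefore reflect a one-arm transition into the next phase, not activity maintained in the preceding one. The 12-month week is not affected.

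The direction and size of any distortion are unknown and cannot be derived from the article. The conclusion rests on two assumptions: that all check-in months are counted from randomisation, and that check-ins take place close to their nominal date. If the full protocol already places the check-in and the change in texts after the wear week, the timing point falls away.

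A reader might also infer that the baseline week has the same problem. It does not: the Randomisation section has all baseline measures completed before randomisation, so baseline wear is already implied to come first.

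**What to change.** Keep the check-in schedule unchanged and move the measurement. Post the accelerometer so that the seven wear days fall before the 3-, 6- and 12-month visit and before any check-in. End the week before the 24-hour exercise restriction in the blood-sampling paragraph of the Assessments section; otherwise, if that restriction precedes sampling as it appears to, about one of the seven days would be suppressed by the protocol itself. At a minimum, state the order of and gap between the wear week and the check-in.

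Add one line to the visit instructions asking both arms to attend blinded assessments without any wrist device, so that blinding does not depend only on participants' silence.

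The cost is postage ahead of each visit and a small risk of late or missed wear. The intervention arm's participant packs already go by post, so mailing to participants is not new to the trial.
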